# Examination

A member of the project team (calibrated examiner) will evaluate the fillings after the

first, second and the fifth year after placement. Criteria (see 16.1) out off the

publication of [name], R. et al. “Recommendations for conducting controlled clinical

Studies of dental restorative materials” (Clin Oral Invest (2007) 11: 5-33) and [name] et al_ FDI World Dental Federation: clinical criteria for the evaluation of direct and indirect restorations – update and clinica lexamples. Clin Oral Invest (2010) 14: 349–366, Appendix) will be used for examination.

The examiners will be calibrated once a year by external examiners. Additional the tool e-calib (www.e-calib.info) has to be used by the examiners for training purposes. The project team will organize the recall of the follow up in the local dental office in collaboration with the dentists.

To reduce costs the participating dentists will evaluate by their own for the baseline,

after the third and forth year. Replicas will be sent to the project team for evaluation.

## Criteria

The criteria of failure are published in [name], R. et al., Clin Oral Invest (2007) 11: 13; Update Clin Oral Investig 2010 14(4), 349-66 and [name] et al_ FDI World Dental Federation: clinical criteria for the evaluation of direct and indirect restorations – update and clinica lexamples. Clin Oral Invest (2010) 14:349–366. Criteria A1, B5, B6, B7, B8, B10, C11, C12 and C13 will be included in the study (See Appenix).

| A1: Surface lustre |
| --- |
| B5: Fracture of material and retention |
| B6: Marginal adaptation |
| B7: Occlusal contour and wear |
| B8: Approximal anatomical form |
| B10: Patient´s view |
| C11: Postoperative sensitivity and tooth vitality |
| C12: Recurrence of caries, erosion, abfraction |
| C13: Tooth integrity |

If the patient will attend between the examination dates, failures will be counted with their first occurrence, documented in patients’ record and study protocol.

For Follow-up explorers (Deppeler, Suisse) will be used: Dental explorer 150 µm and 250 µm, matrix band 50 µm, 100 µm and 150 µm thickness.

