## Follow Up

A Follow up is planned after the first to the fifth year after application. If the filling

failed (see 13.1 Criteria) and has to be replaced, no further follow up will be

necessary.

To reduce costs for examination baseline, third and fourth follow up examination will

be executed by the dentist.

The first, second and fifth follow up examination will be hold by external, calibrated

examiner (dentist), who does intraoral photographs, replica of the shape of the filling

using EXA fast Injection (GC Company) and interponate (Green-bite). Further examination like dental appraisal will not be recorded.

[figure not shown]

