# Interpretation strategy

The adverse event (“Failure”, according to [name], R. et al.) in the study- and control

arm will be calculated in Kaplan/Meier and/or Hazard ratio.

The size of the teeth contact situation in transmission scans will be explored with

GEDAS. The representative randomized selected scan data of the replica gets

matched with the Baseline (Software-Matching) to calculate the volume loss and

height loss in wear characteristics (continuos variables).

Statistical calculation will include descriptive statistics, linear logistic regression,

multivariate logistic regression, Hazard and Kaplan Meyer estimation.

In the case of failure, the patients’ record contains date of failure or date of renewing.

Study relevant clinical record files (CRFs) will be collected at the Greifswald

University and archived for 15 years after study closure.

For the archive contains:

- - Participant signed consent form
  - Insertion RF
  - Follow up RF
  - Occlusal impressions/Interponates
  - Pictures and fotographs
  - Statistical data file and output

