# Cut off points

The study will be suspended if recruitment of dentists will not reach the estimated

numbers per cities during 6-9 month.

The study will be suspended, if failure rate reaches more then 5% of the fillings in the

first year.

The study will be suspended, if response will be below 60% of the examination each

year in respect to the year before.

Not used materials will be sent back to GC.

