## Communications

- Communications with project team during Follow Ups (local dental office)
- Schedule appointments in cooperation with project team
- Rejected appointments
- Communications, if adverse events occur (local dental office)
- Communication with project team
- Communications of project team
- Communications with sponsor
- Communications with local dental office

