## Clinical Record File (CRF, Translation from German)

## Clinical Record File (CRF) Follow Up NU __     ____

| **Dental office ID _****______________** | |
| --- | --- |
| Date of Follow up: |  |
| Patient’s ID: | Pseudonym: |
| No:      Interponat: Replica: | |

| Treatment | 1 | 2 | 3 | 4 |
| --- | --- | --- | --- | --- |
| Tooth |  |  |  |  |
| Surface (S1, S2, S2mod) |  |  |  |  |
| A1  Surface lustre |  |  |  |  |
| B5  Fracture of material and retention |  |  |  |  |
| B6  Marginal adaptation |  |  |  |  |
| B7  Occlusal contour and wear |  |  |  |  |
| B8  Approximal anatomical form |  |  |  |  |
| B10  Patient’s view |  |  |  |  |
| C11  Postoperative (hyper-)sensitivity and tooth vitality |  |  |  |  |
| C12  Recurrence of caries (CAR), erosion, abfraction |  |  |  |  |
| C13  Tooth integrity |  |  |  |  |

See: [name] et al

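### Between examinations the protocol collects failures but no date on which a filling was last seen intact, so Kaplan-Meier can overstate failure among patients who stop attending study examinations

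*Protocol*

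**What the plan says.** Under Examination, Criteria: "If the patient will attend between the examination dates, failures will be counted with their first occurrence". Under Interpretation strategy: "In the case of failure, the patients’ record contains date of failure or date of renewing". That section also calls failure the adverse event of the study, and says that failure in the study and control "arm will be calculated in Kaplan/Meier and/or Hazard ratio". Responsibilities and Communications have the local office report adverse events to the project group.

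Scheduled information comes from the yearly visits: "A Follow up is planned after the first to the fifth year after application". External examiners hold years 1, 2 and 5; the practice dentist does baseline and years 3 and 4. The follow-up form in the Appendix carries one date, "Date of Follow up", and the scores for that visit. Cut off points suspends the study only if response falls below 60% of the year before, so a yearly loss of up to 40% is tolerated.

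No section asks the office to report an intact filling seen at an attendance outside these examinations. No section states when a non-attender is censored.

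**The concern.** There are two routes into the data between examinations, and only failures have both. Patients belong to the practice, so someone can decline further study examinations and still see the same dentist. If the filling later fails, the failure can be counted. If it survives, the last date known intact is the last examination attended.

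Censoring at that examination would then depend on the later outcome: of the fillings no longer examined, only those that go on to fail stay in the risk set. Kaplan-Meier and the hazard ratio assume that this does not happen. Comparing survival rates is the first aim of the trial, so the absolute survival figures are what is at stake.

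**Working it through.** **Where the 11% comes from.** Calculation of the participants uses hazards 0.0201 and 0.0268 per month, 12 months of accrual, 60 months in total, 90% power, two-sided 0.05 and a dropout rate of 1% with no time unit. Take n = (1.960 + 1.282)² (1/p1 + 1/p2) / ln(0.75)², where p is the probability of an observed event. With dropout 0.01 per month, p1 = 0.536 and p2 = 0.628, so n = 439, matching the stated 440. With 1% per year, n = 365. A rate of 0.01 per month is 1 − exp(−0.12) = 11.3% per year. I use it as an illustrative rate of leaving the examinations; the protocol does not give that rate.

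**Formula.** Assume exponential failure, attendance independent of failure, and failures dated correctly. Let F be true five-year failure and s = (1 − F)^(1/5). Let a_k be the share whose last attended examination is year k or later, and c the share of failures after the last attended examination that still reach the study. Fillings without a reported failure are censored at the last attended examination. In year k:

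- events: d_k = [a_k + c(1 − a_k)] (s^(k−1) − s^k)
- at risk: n_k = a_k s^(k−1) + c(1 − a_k)(s^(k−1) − s^5)
- Kaplan-Meier failure: 1 − Π(1 − d_k/n_k)

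The second term of n_k is the fault: patients past their last examination are at risk only if they will fail by year five. If c = 0, d_k/n_k = 1 − s, the truth. If the same patients also supply intact dates, the term becomes c(1 − a_k)s^(k−1), and the ratio is again 1 − s.

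**Worked case.** F = 0.20, so s = 0.9564; permanent loss m = 0.113, so a_k = (1 − m)^k; c = 0.5. The true yearly ratio is 0.0436.

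| Year | a_k | d_k | n_k | d_k/n_k |
|---|---|---|---|---|
| 1 | 0.887 | 0.0412 | 0.898 | 0.0458 |
| 2 | 0.787 | 0.0373 | 0.769 | 0.0485 |
| 3 | 0.698 | 0.0339 | 0.655 | 0.0517 |
| 4 | 0.619 | 0.0309 | 0.556 | 0.0556 |
| 5 | 0.549 | 0.0283 | 0.467 | 0.0605 |

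The product of (1 − d_k/n_k) is 0.764, so estimated failure is 23.6% against a true 20%.

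**Range.** For patients who miss at random and may return, a_k = 1 − m^(6−k). Entries are estimated failure when the truth is 20%/30%.

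| Missed per year | Pattern | c = 0.5 | c = 1 |
|---|---|---|---|
| 1% | permanent | 20.3/30.3 | 20.5/30.7 |
| 11.3% | permanent | 23.6/34.7 | 27.0/39.0 |
| 20% | permanent | 28.0/40.3 | 34.8/48.3 |
| 40% | permanent | 48.9/63.3 | 63.8/76.5 |
| 11.3% | return | 20.3/30.3 | 20.5/30.7 |
| 20% | return | 20.5/30.7 | 21.0/31.4 |
| 40% | return | 21.6/32.2 | 23.2/34.3 |

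The stated hazards imply true failure of 70%/80%. At 11.3% permanent loss they give 74.9%/83.7% (c = 0.5) and 78.5%/86.4% (c = 1). Simulation with 400,000 fillings per cell agrees with these results to within sampling error.

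**Arm comparison.** At 11.3% permanent loss the ratio of events per time moves from 0.750 to 0.766 (c = 0.5) or 0.779 (c = 1). In the 20%/30% case it moves from 0.626 to 0.633 or 0.641. At 40% permanent loss, 0.75 becomes 0.82 to 0.85.

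**The case against.** The strongest reply is that the protocol sets no censoring date and does not say whether a failure after a missed examination counts. A statistical analysis plan may settle both, and ending follow-up symmetrically would remove the bias. That stands: the documents allow the bias but do not prove it. What an analysis plan cannot do is use dates that nobody was asked to send. Without them it must set aside failures that the Criteria section says are to be counted. Charts could be searched later, so the loss is not irreparable, but the list linking pseudonyms to patients stays in the office and the search would have to go through it.

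A reader might infer that offices never report an intact filling. They do, at baseline and years 3 and 4, and no visit window is stated, so a late attendance might be recorded as one of those examinations. A reader might also infer that everyone who misses an examination is affected. A patient who attends a later one gets full survivor credit, and the return rows above show how little bias remains.

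The dropout rate in the sample-size section means loss to observation, which is c = 0 and no bias. Using it for patients whose failures are still seen is an assumption.

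Finally, both arms are affected alike. At 11.3% permanent loss and c = 0.5, the expected z for the log rate ratio with 440 per arm is about 3.2, whether the extra failures are counted or dropped. In the 20%/30% case counting them raises it from about 2.9 to 3.1. The ratio is pulled slightly toward 1, but the documents do not support a claim that the comparison of materials is undermined.

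**Conclusion.** The point holds as a gap in data collection. Outside scheduled examinations the protocol collects failures and no intact dates. For patients who stop attending examinations but stay with the practice, censoring at the last examination while counting later failures overstates failure in both arms.

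The overstatement is about 4 to 9 points at 11% permanent loss per year with half to all later failures reported, when true failure is 20%/30%. It is under 1 point at 1% loss and zero if no later failures are reported. It exceeds 40 points only if the full tolerated 40% is lost permanently each year. Where patients miss at random and return, with half of otherwise unseen failures reported, it is about 1 point or less at 11% to 20% missed and about 2 points at 40%. The share permanently absent and the share reported are both assumed. The harm is to the absolute survival rates; the hazard ratio is little changed at moderate loss. The protocol does not fix the bias in place, because it states no censoring rule.

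**What to change.** Add to Criteria and Follow Up: for each study filling whose patient missed a yearly examination, the office returns from its chart the date the patient was last seen and whether the filling was in place. Use that date as the end of observation. This restores the true value when the patients whose failures would be reported also supply intact dates; if attendance is prompted by the failure itself, some bias remains.

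Where no such date exists, end follow-up in the main analysis at the last attended examination for failures and survivors alike, which removes the bias. Cutting off only after the first missed examination is not enough: at 11.3% permanent loss and c = 0.5 it still gives about 21%/32%. Report the analysis that counts every failure found between examinations as a sensitivity analysis.

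The cost is a short amendment and a brief chart query per missed visit. If the fallback applied to everyone, some reported failures would be lost. In the worked case, failures up to the last attended examination number 440 × Σ a_k(s^(k−1) − s^k) = 440 × 0.143 = 63 per arm, against 440 × [0.143 + 0.5 × (0.200 − 0.143)] = 75 if later reports are counted.

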## Examination after application of the filling

The data files (Screening, questionnaire) and baseline impression will be sent by mail

to the project team for analysis by scanning. The data files create a data base (Stata

10.1). All impressions will be scanned (transmission and surface scan). Transmission

scans gets analysed with GEDAS tool *(Hützen D, Proff P, Gedrange T, [name] R, Bernhard O, Kocher T, Kordass B: Occlusal contact patterns – population-based data. Ann Anat. 2007;189(4): 407-11; Hützen D, Rebau M, Kordass B: Clinical reproducibility of GEDAS – „Greifswald Digital Analysing System“ for displaying occlusal patterns. Int J Comput Dent 2006 Apr;9(2):137-142. )*

The measurements include the isthmus thickness in extend and depth of the occlusal

surface to the mesial or distal preparation by di- and trihedral fillings. For evaluation

greater fillings (more then trihedal) only the box preparation can be counted.

Randomly selected replica of case- and control arm will be scanned (3DLaserscan/

SmartOptics, accuracy < 20 µm).

## Follow Up

A Follow up is planned after the first to the fifth year after application. If the filling

failed (see 13.1 Criteria) and has to be replaced, no further follow up will be

necessary.

To reduce costs for examination baseline, third and fourth follow up examination will

be executed by the dentist.

The first, second and fifth follow up examination will be hold by external, calibrated

examiner (dentist), who does intraoral photographs, replica of the shape of the filling

using EXA fast Injection (GC Company) and interponate (Green-bite). Further examination like dental appraisal will not be recorded.

[figure not shown]

# Interpretation strategy

The adverse event (“Failure”, according to [name], R. et al.) in the study- and control

arm will be calculated in Kaplan/Meier and/or Hazard ratio.

The size of the teeth contact situation in transmission scans will be explored with

GEDAS. The representative randomized selected scan data of the replica gets

matched with the Baseline (Software-Matching) to calculate the volume loss and

height loss in wear characteristics (continuos variables).

Statistical calculation will include descriptive statistics, linear logistic regression,

multivariate logistic regression, Hazard and Kaplan Meyer estimation.

In the case of failure, the patients’ record contains date of failure or date of renewing.

Study relevant clinical record files (CRFs) will be collected at the Greifswald

University and archived for 15 years after study closure.

For the archive contains:

- - Participant signed consent form
  - Insertion RF
  - Follow up RF
  - Occlusal impressions/Interponates
  - Pictures and fotographs
  - Statistical data file and output

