# Calculation of the participants

The calculation of the numbers of participants were done with „nQuery 4.0“ software

by [name]. [name].

As aim (dependent variables) were used

- Loss of filling (dichotomy variable), defined as fracture or crack of the filling
- Abrasion of the occluded filled surfaces (scaled variable)
- Wear abrasion of the occlusal surface (scaled variable)

When the sample size in each group (Fuji IX and Equia) is 440, an exponential

maximum likelihood test of equality of survival curves with a p= 0.050 two-sided

significance level will have 90% power to detect the difference between a Group 1

exponential parameter, .1 of 20 % 0.0201 (corresponding to a proportion of 30% after

60 months) and a Group 2 exponential parameter, .2 of 0.0268 (corresponding to a

proportion of 20% after 60 months and a constant hazard ratio of

0.0201/0.0268=0.75) 30 %. This assumes an accrual period of 12 months, a

maximum follow-up time of 60 months (five years), and a common exponential

dropout rate of 1%.

The calculation is based on all incorporated units (fillings), e.g. all possible units

(fillings). The homogeneity of the participants will be guaranteed by the recruiting

phase, which will use the following selection criteria: Only one (at most two)

restoration for each side is calculated for each patient. The restoration will be limited

to posterior teeth (premolars and/or molars).

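### The late wear comparison is conditional on the filling surviving, while wear can itself be a failure; if fillings are replaced for wear, the year-5 difference can be distorted

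*Protocol*

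**What the plan says.** Comparing the wear of the two materials is the second aim (Protocol, Aims of the Study), and wear is a scaled dependent variable in Calculation of the participants.

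- **Measurement.** Under Examination after application of the filling: "Randomly selected replica of case- and control arm will be scanned". Under Interpretation strategy the selected scans are "matched with the Baseline (Software-Matching) to calculate the volume loss and" height loss. The unit that is drawn is the replica, not the filling placed.
- **Failure.** The Criteria section introduces its list as criteria of failure, and the list contains "B7: Occlusal contour and wear".
- **End of follow-up.** Under Follow Up, for a filling that "failed (see 13.1 Criteria) and has to be replaced, no further follow up will be" needed.
- **A different definition.** Calculation of the participants defines loss of a filling as fracture or crack only and lists wear separately.

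The protocol states no wear difference, no spread of wear and no share of failures expected from B7.

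**The concern.** A replaced filling yields no later replica. If it was replaced because it had worn too far, it is absent from the later wear data because of the very quantity being measured. A random draw from the replicas that remain is then a random sample of surviving fillings, not of the fillings placed. If one material wears faster and both are replaced at about the same amount of wear, more of its worst fillings drop out and the late averages move together. The trial could then report similar year-5 wear for materials that differ, with part of the difference visible only in the failure endpoint.

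**Working it through.** **1. The plan's own figure.** There is none for wear. The survival calculation matters here because it sets how many fillings are still in place late on. Its inputs, all from Calculation of the participants: 440 fillings per arm, 90% power and a two-sided 5% level; monthly hazards of 0.0201 and 0.0268; follow-up of at most 60 months, of which 12 are accrual; dropout 1% with no time unit. The first hazard is printed as "exponential parameter, .1 of 20 % 0.0201 (corresponding to a proportion of 30% after", so a 20% and a 30% stand beside the same parameter. Taking dropout as η = 0.01 per month, the probability of an observed event is

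E(λ) = λ/(λ+η) × {1 − [exp(−48(λ+η)) − exp(−60(λ+η))] / [12(λ+η)]}

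- λ = 0.0201: (0.0201/0.0301) × (1 − 0.198) = 0.536
- λ = 0.0268: (0.0268/0.0368) × (1 − 0.138) = 0.628

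n per arm = (1.960 + 1.282)² × (1/0.536 + 1/0.628) / (ln 0.75)² = 10.507 × 3.460 / 0.08276 ≈ 439, so 440 is reproduced. The form on the hazard scale gives 442, with power 0.899 at 440. Dropout of 1% per year would give 368.

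**2. Fillings with no year-5 replica because of failure** (440 per arm, no dropout).

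- Stated hazards: 440 × exp(−0.0201 × 60) = 132 and 440 × exp(−0.0268 × 60) = 88 in place, so 70% and 80% have failed.
- If the printed 20% and 30% are instead 5-year failure rates: 440 × 0.80 = 352 and 440 × 0.70 = 308 in place.

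On either reading the loss is substantial and unequal by arm. It biases wear only in so far as it is related to wear.

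**3. Size under assumed values.** Not from the protocol: wear linear in time, lognormal rates with coefficient of variation (CV) 0.5 in both arms, mean wear 25% higher in one arm, failure at one common wear limit, and independent other failures of 20% by year 5. Simulation with 400,000 fillings per arm:

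| Fillings past the wear limit by year 5 (pooled) | Year-5 difference among survivors | Share of the true 25% |
| --- | --- | --- |
| 5% | 18.7% | 0.187/0.25 = 0.75 |
| 10% | 15.7% | 0.63 |
| 20% | 12.4% | 0.50 |
| 30% | 10.4% | 0.42 |
| 50% | 7.2% | 0.29 |

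Across these rows the difference is about 25% at year 1 and 20–25% at year 2. Total 5-year failure implied by the first two rows is 1 − 0.95 × 0.80 = 24% and 1 − 0.90 × 0.80 = 28%. From the third row on it is 36% or more (1 − 0.80 × 0.80), which fits only the 70–80% reading of step 2.

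**4. A second set of assumptions.** Mean wear ratio 1.3, CV 0.5, other failures independent of wear with hazard ratio 0.75, 1,000,000 fillings per arm. Share of the true year-5 difference still visible:

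| Share of control failures due to wear | Control failure 30% | Control failure 80% |
| --- | --- | --- |
| 0% | 1.00 | 0.99 |
| 5% | 0.90 | 0.81 |
| 10% | 0.84 | 0.69 |
| 25% | 0.71 | 0.51 |
| 50% | 0.57 | 0.32 |

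At year 1 the share is about 1.00 throughout. At year 3, with 25% of control failures due to wear, it is 0.95 and 0.85.

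**5. What changes the answer.**

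- If a replica is kept at the visit where the wear failure is found, the 25% row improves to 0.84 and 0.67.
- If the better material has the wider spread (CV 0.9 against 0.3; control failure 30%, a quarter of it from wear), the year-5 difference grows to 1.58 times the truth.

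**The case against.** A reader might infer that the plan loses its most worn fillings and so biases the wear comparison toward no difference. The protocol does not support that as a statement of fact, for four reasons.

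- **Wear may not end follow-up at all.** If loss means fracture or crack, as in Calculation of the participants, the mechanism disappears. The Criteria list also contains surface lustre and patient's view, so it can be read as the set of graded items on the record form. The grade of B7 that counts as failure lies in cited publications and figures that are not shown. This stands as a reason for caution. Against it, Follow Up and Interpretation strategy, which govern observation and analysis, refer to the Criteria section and to the published failure criteria, not to the narrower definition.
- **Replacement is also required.** A poor B7 score alone does not remove a filling. This stands.
- **Failed fillings do have replicas.** Baseline and earlier yearly replicas exist, and nothing forbids one at the scheduled visit where failure is found. This stands and reduces the loss (step 5). For failures between visits the protocol asks for counting and documentation but mentions no replica.
- **Time point and estimator belong to an analysis plan.** Agreed: silence on them is not the point here. The protocol itself fixes the replica as the sampling unit and fixes the end of follow-up, and no later analysis can recover a replica that was never taken.

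Direction and size also depend on quantities the protocol does not give: with no wear failures there is no such bias, and with unequal spread it can enlarge the difference. The simulated figures are illustrations, not estimates for this trial.

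**Conclusion.** The point holds conditionally. If fillings are replaced because of wear, the late replica-based comparison, above all at year 5, describes surviving fillings only and can be distorted; choosing replicas at random does not correct this. With one wear limit and similar spread in both arms the difference shrinks: an assumed 25% becomes about 19% with 5% wear failures by year 5 and about 16% with 10%. Year 1 is practically unaffected and year 2 little affected.

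Separately, and without any assumption, the protocol contradicts itself on whether wear is a failure, and the sections must be reconciled. The matter concerns a secondary aim and should be corrected, with medium confidence because the share of B7 failures is unknown.

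**What to change.** 1. Reconcile the definition of loss in Calculation of the participants with Criteria, Follow Up and Interpretation strategy, so that it is clear whether a B7 finding can be a failure.
2. In Examination after application of the filling and in Interpretation strategy, draw the random wear sample by arm from the fillings placed, and scan all available replicas of those fillings up to the last one before failure.
3. At later visits, alongside mean height and volume loss in surviving fillings, compare the arms by ranks with fillings that failed on B7 ranked worst. Under a common wear limit each such filling has worn more than every survivor, so the worst rank largely restores the contrast between arms.
4. Report B7 failures by arm, and label the survivors-only mean as conditional on survival.
5. Report years 1 and 2 as the least depleted comparison. They need not replace year 5 as the main one; doing so would give up the long-term contrast.

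Replicas are already planned at baseline and every yearly visit, so no new clinical procedure is needed. The cost is revised wording, some additional scanning, and a rank result that is not expressed in micrometres.
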